## Abstract

**Background:**

Cognitive impairment and neuropsychiatric syndromes, like depression and apathy, are frequent residual consequences of stroke. These have a large impact on quality of life and long-term prognosis. Several factors are involved in the development of these residual syndromes, although their exact role and their interrelationships remain still rather unclear. The Cognition and Affect after Stroke: a Prospective Evaluation of Risks (CASPER) study has been primarily designed to examine whether stroke-specific (e.g. lesion location, volume, type, severity), cerebrovascular and neurodegenerative (e.g. white matter changes, atrophy, microbleeds, perivascular spaces), inflammatory, endothelial, and (epi)genetic markers are associated with cognitive impairment, post-stroke depression, and post-stroke apathy, and whether they predict their course over 12 months. The secondary aims are to investigate how the above-mentioned markers interact with each other, and to determine if patients with apathy and depression after stroke differ in pathogenesis, course, and outcome (e.g. functional outcome, neurocognitive performance, quality of life).

**Methods/design:**

CASPER is a 1-year prospective clinical cohort follow-up study in 250 stroke patients recruited at the neurological in- and outpatient services at Maastricht University Medical Center (MUMC+, Maastricht, The Netherlands), and Zuyderland Medical Center (Sittard and Heerlen, The Netherlands). At baseline (3 months post-stroke), a neuropsychological assessment, neuropsychiatric interview, blood sample, and brain magnetic resonance imaging (MRI) scan are conducted. Assessment of neuropsychiatric and neurocognitive status are repeated 6 and 12 months later.

**Discussion:**

The CASPER study investigates stroke-specific, vascular, neurodegenerative, inflammatory, and genetic markers of the development of vascular cognitive impairment, depression, and apathy after stroke. This creates the possibility to study not only the contribution of these individual markers but also their joint contribution, which differentiates this study from earlier stroke cohorts who lacked long-term follow-up data, a large sample size, an extensive MRI protocol, and markers from the blood. The knowledge we derive from this study might help in identifying markers that are associated with, or can predict the onset, maintenance, and progression of vascular cognitive impairment, depression, and apathy after stroke, and could provide new insights into possibilities for treatment and rehabilitation that result in better functional outcome after stroke.

**Trial registration:**

ClinicalTrials.gov NCT02585349

## Background

Stroke is one of the leading causes of disability in the Western world. According to the Global Burden of Disease Study in 2010 the stroke incidence worldwide was around 17 million persons per year, with 33 million people being still alive after stroke, with about 70 % of all stroke patients staying with residual symptoms [1]. Stroke is the second most frequent cause of death, after coronary artery disease [2]. As a result of the aging population, this number will probably increase steadily in the next decades [3]. At the same time, case fatality rates are declining due to better acute treatment. Therefore, more and more individuals will need to learn how to deal with the residual disabilities and handicaps [1]. Frequent impairments after stroke are cognitive impairments and neuropsychiatric syndromes, including depression and apathy [4, 5] which have an impact on long-term prognosis (higher mortality and more disability) and quality of life (QoL) of stroke survivors [6, 7].

### Vascular cognitive impairment

Vascular cognitive impairment (VCI) describes the full spectrum from mild to severe cognitive impairment in people with cerebrovascular disease, including vascular mild cognitive impairment and vascular (or post-stroke) dementia (VaD) [8]. Risk factors of VCI after stroke include event-related factors such as infarct severity, lesion volume, age, low education, history of diabetes or atrial fibrillation, and number of recurrent strokes [9]. The risk for post-stroke dementia is known to be highest within the first year, with an estimated incidence rate of 20–30%, which is nine-times the general population’s risk [9].

It has been suggested that both vascular and neurodegenerative pathologies contribute to post-stroke VCI [10]. Cognitive impairments can be the result of strategic infarcts, but (pre-existing) white matter hyperintensities (WMH) and atrophy of the medial temporal lobes can contribute too, and they probably interact with each other, though the nature of these interactions is not well understood [11]. In addition, a higher risk for VCI has been reported in carriers of the Apolipoprotein E (ApoE) ε4 allele, which is the major genetic risk factor for Alzheimer’s disease (AD) dementia [12]. Indeed, evidence accumulates that AD and VaD should not be regarded as mutually exclusive diagnoses, but rather as a continuum with pure AD and VaD at its extremes, and most people showing mixtures of both type of pathologies [13]. While the dominating view is that vascular changes work as a catalyst of primary neurodegenerative changes in AD it is largely unknown whether the opposite is true for VCI, i.e. whether AD-related changes work as a catalyst for post-stroke dementia.

Next to neurodegeneration, neuro- and vascular inflammation might contribute to VCI by partly mediating the pathophysiology underlying VCI as part of a final common pathway [14]. Following stroke, increased auto-immune activity is a common response, and it has been shown that up-regulated inflammation markers like C-reactive protein (CRP), as a consequence of a prolonged auto-immune response, relate to poor prognosis. This includes a higher risk of additional future strokes and mortality, but also more severe VCI [15, 16]. Other enzymes, molecules, and ligands (myeloperoxidase, soluble intercellular adhesion molecule, soluble vascular cell adhesion molecule-1, soluble E selectin, soluble P selectin and CD40 ligand) are involved in vascular inflammation as part of an inflammatory response to stroke, and have also been found to be increased in AD [17–20]. Also, up-regulation of proinflammatory cytokines (interleukin-6 and tumor necrosis factor alpha) and proteins (high sensitivity CRP) are risk factors for both dementia [21, 22] and cardiovascular disease [23]. It is unknown whether similar inflammation mechanisms are involved in cognitive deterioration in VCI, and therefore, research is needed to investigate whether inflammation contributes to VCI independently or in joint action with other (e.g. neurodegenerative) factors.

Finally, genetic factors are also suggested to play a role in the pathogenesis of VCI, but in contrast to AD, evidence is still scarce. A genome-wide association study in VaD identified a novel genetic locus near the androgyn receptor, and this finding was replicated in two independent validation datasets [24]. Polymorphisms and mutations on the genes coding for angiotensin-converting enzyme and methylenetetrahydrofolate reductase are risk factors for cardiovascular diseases and might be related to the development of VaD, although this relationship is still controversial [25]. For AD, several genetic risk loci are already identified next to ApoE, including clusterin (CLU), phosphatidylinositol binding clathrin assembly protein (PICALM), and encoding complement component [3b/4b] receptor 1 (CR1) [26], but their effects are generally small (see http://www.alzgene.org). Whether they contribute to post-stroke dementia is not known.

### Post-stroke depression

Depression is a common neuropsychiatric syndrome following stroke. According to a recent systematic review by Hackett et al. [27], around one-third of the stroke survivors experiences depression in the first 3 months post-stroke, and studies with long-term follow-up have shown that it is often a chronic disorder, with a remitting-relapsing pattern [28]. Patients with post-stroke depression (PSD) have worse functional recovery [29], a higher risk for cognitive impairment [7], and higher mortality risk [30, 31].

Early studies implied that PSD is mainly associated with anterior lesions in the left hemisphere, however, a major systematic review and meta-analysis found no support for this ‘lesions location hypothesis’ [32]. Vataja et al. [33] suggested that lesions in fronto-subcortical regions in general are involved in developing PSD, often accompanied by impairments in executive functioning, leading to what has been called the ‘depression-executive dysfunction syndrome’. Other factors that have been associated with the development of PSD are cognitive impairment, stroke severity, physicial disability, and pre-stroke depression and anxiety [7]. Diminished QoL and also low social support can both contribute independently to the severity of depression [34]. A study by van Mierlo et al. [35] investigated the association between a broad range of psychological factors and PSD with a multivariable logistic regression analysis. They showed that more passive coping and more helplessness, less acceptance and less perceived benefits were all significantly and independently associated with symptoms of post-stroke depression. Furthermore, fatigue after stroke has been associated with PSD, although not all patients with fatigue develop symptoms of depression and vice versa [28].

Neuroinflammation might also play a role in the underlying mechanisms of PSD. Levels of CRP, soluble E selectin, CD40 ligand, interleukin-6, tumor necrosis factor alpha, and high sensitivity CRP are deregulated in patients diagnosed with major depressive disorder [14, 18, 22, 23, 36–38]. In addition, high plasma levels of neopterin are found in people with depression, and might predict the development of PSD [39]. Markers of endothelial function might be important as well, since increased expression of soluble intercellular adhesion molecule and soluble vascular cell adhesion molecule-1 are associated with depression [40–43]. Although several inflammation markers have been related to symptoms of depression, studies examining these associations in PSD specifically are relatively scarce. Some studies found an elevation in interleukin-6 and tumor necrosis factor alpha in PSD [44]. Recently, a study by Tang et al. [39] showed an association between elevated serum levels of neopterin in the acute phase after stroke and PSD at 6-month follow-up.

High plasma levels of homocysteine are known to increase the risk for cerebrovascular disease, but have also been associated with depressive disorders. Increased levels of homocysteine result in cerebrovascular disease and a deficiency in monoamine neurotransmitters, which might lead to a depressed mood [45]. Homocysteine, folate and vitamin B12 are all involved in methylation reactions that are necessary for monoamine neurotransmitter production, but also the production of phospholipids and nucleotides. A deficiency in folate and vitamin B12 has also been associated with depressive disorders [46].

### Post-stroke apathy

Apathy has been defined as a disorder of diminished motivation, characterized by lowered initiative, restricted engagement in social interactions and activities, diminished cognitive activities, and lack of emotional response [47]. It was traditionally seen as a symptom of other syndromes (e.g. depression and dementia), but mounting evidence suggests that it might be an independent syndrome with a different etiology [48–50]. Post-stroke apathy (PSA) is as frequent as PSD, with a mean prevalence rate of 34.6 % at 4 months post-stroke [5]. However, PSA gained relatively less attention in research in comparison with PSD, and most research focuses on the difference between the two.

While PSD is suggested to be associated with left anterior lesions [51, 52], PSA has been associated with right hemispheric subcortical lesions, particularly in the basal ganglia and in the anterior cingulate circuit which is involved in motivational processes [53–55]. Other factors associated with PSA are older age, lower education, and severity of VCI [4, 5, 51, 56]. Furthermore, both PSD and PSA have been associated with poor functional recovery and low QoL [5, 29]. Overall, lack of longitudinal studies, differences between time of measurement after stroke (acute phase/chronic phase), and lack of studies with a sufficient sample size make it difficult to interpret study results.

In conclusion, several factors play a role in the development of VCI, PSD, and PSA. However, most studies investigated the underlying mechanisms in isolation and did not take into account how several factors interact with each other. The Cognition and Affect after Stroke, a Prospective Evaluation of Risks (CASPER) study incorporates a broad range of psychosocial, blood and neuroimaging markers to be able to study their role alone and in combination with each other to predict individual differences in the onset and course of the cognitive and neuropsychiatric consequences of stroke.

### Study aims

The primary aim of CASPER is to identify stroke-related, cerebrovascular, neurodegenerative, (epi)genetic, endothelial and inflammation markers that are associated with VCI, PSD, and PSA in patients with ischemic or hemorrhagic stroke. The secondary aims are to investigate how the above-mentioned markers interact with each other, and to determine if patients with apathy and depression after stroke differ in pathogenesis, course, and outcome (e.g. functional outcome, neurocognitive performance, quality of life).

The main research questions are:Are stroke-specific, additional vascular, neurodegenerative, inflammatory or genetic markers a) associated with VCI at 3 months after stroke and b) predictive for its course over 12 months?Are stroke-specific, additional vascular, neurodegenerative, inflammatory or genetic markers a) associated with PSD and PSA at 3 months after stroke and b) predictive for their course over 12 months?Do the above-mentioned markers interact on VCI, PSD, and PSA outcome?Which psychosocial factors are associated with the development of VCI, PSD, and PSA?Do PSA and PSD differ in their pathogenesis, cognitive profile, course, and outcome?

## Methods

### Study design

CASPER is a prospective clinical cohort study into cognitive impairments and neuropsychiatric syndromes after stroke with a follow-up of 1 year. Baseline measurements take place in the post-acute phase after stroke (i.e. 10 to 12 weeks post-stroke) to assess presence and severity of VCI, PSD, and PSA. Serial assessments take place at 6 and 12 months after baseline. The total duration of the study will be approximately 3.5 years, from June 2013 (first in) until November 2016 (last out).

### Patients

In total, 250 consecutive patients with either ischemic or hemorrhagic stroke are included. Patients who are admitted to the Stroke Unit of the Maastricht University Medical Center + (MUMC+), Maastricht, the Netherlands, the Stroke Unit of Zuyderland Medical Center in Sittard-Geleen and Heerlen, the Netherlands, or those who visit the Transient Ischemic Attack clinic of MUMC+ for a non-fatal ischemic or intracerebral hemorrhagic stroke and fulfill the in- and exclusion criteria are asked to participate. Stroke is defined as a clinical stroke syndrome (sudden neurological dysfunction lasting >24 h, with no apparent cause other than that of vascular origin). The stroke can be a first-ever event or a recurrent supra- or infratentorial stroke in a patient who recovered from a previous event without obvious residual symptoms. Ischemic strokes might be cortical or lacunar, and could be included with or without evidence of ischemia on clinical brain scan. Hemorrhagic strokes are non-traumatic deep, lobar, cerebellar, or brainstem hemorrhages as evidenced by a clinical brain scan. Eligibility criteria are chosen to make sure that the sample will represent the current clinical situation (Table 1). Participation of an informant who knows the patient well enough to answer questions about his/her functioning over the last ± 10 years is desirable but not required.

**Table 1 Tab1:** In- and exclusion criteria

Inclusion criteria	Exclusion criteria
- Ischemic or hemorrhagic stroke	- Subarachnoidal hemorrhage, traumatic hemorrhage, primary intraventricular hemorrhage and transient ischemic attack
- MMSE score ≥ 15 (to ensure valid testing)	- Age younger than 40 years (to exclude atypical strokes)
- Written informed consent	- Severe aphasia (as it interferes with performance on and understanding of the instructions of the neuropsychological tests)
- Sufficient knowledge of the Dutch language	- Evidence for pre-stroke dementia (based on clinical diagnosis or IQ-CODE) in the 5 years prior to the stroke
	- Other existing psychiatric and neurological diagnoses that are known to affect cognition (Parkinson’s disease, bipolar disorder, epilepsy, schizophrenia, or substance abuse)^a^

^a^Lifetime history of depression is not considered as a reason for exclusion as it might be a risk factor for post-stroke depression

### Assessments

The baseline measurement (T0) is scheduled 3 months post-stroke to avoid confounding effects by the acute event, including acute inflammatory responses. At T0, patients undergo a venipuncture, brain magnetic resonance imaging (MRI) scan, neuropsychological assessment and neuropsychiatric interview. They fill in several questionnaires to assess the presence and severity of PSD and PSA, and to evaluate other factors as functional ability, fatigue, personality, and QoL. A semi-structured interview with an informant is performed to provide additional information about functional outcome of the patient and presence of neuropsychiatric syndromes. Six (T1) and 12 months (T2) after T0, the neuropsychological assessment and questionnaires are repeated. The venipuncture, MRI scan, neuropsychological assessment, and neuropsychiatric interview all take place in the academic hospital in Maastricht and are performed by specially trained nurses (venipuncture), radiology assistants (MRI scan) and trained research (neuro)psychologists (neuropsychological assessment and neuropsychiatric interview). If a patient is not able to visit the hospital due to reduced mobility, the patients are visited at their current place of residence.

Patients who suffer from a recurrent stroke during the 12-month follow-up period will be followed-up normally, if the health status of the patient allows this, and if the patient does not suffer from severe aphasia after the recurrent stroke. Information about the type, location, and severity of the lesion of the recurrent stroke is collected, which also allows us to study the potential impact of recurrent strokes on our outcome measures. Recurrent strokes are taken into account in our analyses with longitudinal data to avoid confounding effects.

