### Power calculation and sample size

Based on results of the CODAS study [86], a previous study with stroke patients of our research group, it is expected that 50 % of the stroke patients will have VCI and 10 % will have VaD after 1 year. Furthermore, it is expected that 35 % of the patients will have minor or major depression after 1 year post-stroke [87]. A power calculation was performed with the freeware program G*Power version 3.1 (http://www.gpower.hhu.de) assuming categorical independent variables to which 50 % are exposed and 50 % are not exposed (median-split), since no reliable estimates are available for our main predictors from literature (MRI, inflammation, and genetics). Based on a 1-year follow-up, a two-sided alpha level of .05, and an expected drop-out rate of 20 % based on the CODAS study (about 10 % due to death), a sample size of 250 resulted in a power of 86 % to detect a relative risk of 2.00, or 80 % to detect a relative risk of 1.89 for PSD, and a 96 % power to detect a relative risk of 2.00, or 80 % power to detect a relative risk of 1.70 for VCI.

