However, some limitations of the study protocol have to be acknowledged here. Although the extensive in- and exclusion criteria were formulated with caution, they can possibly result in a less representative group of patients compared to the general stroke population. For instance, patients who are aphasic or who have pre-existent cognitive disturbances are excluded. No data are collected in the acute phase after stroke, which could yield additional information on the association between VCI, PSD, PSA and the earlier mentioned investigated markers, but a post-acute baseline time point is chosen to avoid confounding effects in the acute phase (e.g. generic acute inflammatory response, sickness behavior). MRI scans and venipuncture are only performed on T0, since it is not feasible due to logistical and financial reasons to repeat them at T1 and T2. However, if these data could also have been collected more information on the causes of VCI, PSD, and PSA could have been gathered, e.g. by linking longitudinal changes on MRI to changes in outcomes. Furthermore, patients with severe stroke are less probable to participate in the study, as the assessment is quite extensive. This can result in a cohort of patients with relatively mild stroke, which may influence the frequency of VCI, PSD, and PSA. Both ischemic and hemorrhagic strokes are included to increase the inclusion rate, however, due to the different etiologies of these strokes, it is likely that this limits the generalizability of the results. Therefore, we have to correct for stroke type in our analyses to take this into account. It is also likely that patients with depression or apathy after stroke are less motivated to participate in the study, resulting in an underestimation of the PSD and PSA prevalence in the study sample. In addition, the current follow-up period of 1 year allows testing predictions in the post-acute to early chronic phase, but is too short to study long-term consequences. Finally, CASPER allows for in-depth phenotyping and also covers a broad spectrum of factors impacting on the consequences of stroke, but it is not powered to test for more subtle associations or to use complex genetic models or testing of rare variants. Therefore, the study is also designed as to allow harmonization with other stroke cohorts in larger meta-studies as part of the STROKOG consortium (https://cheba.unsw.edu.au/group/strokog).

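### Recurrent stroke after T0 is handled as a confounder, but it cannot confound markers measured at T0; for inflammation markers and VCI it is a plausible mediator

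*Protocol article*

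**What the plan says.** The Assessments section of the protocol article sets the rule for follow-up strokes. On conduct: "Patients who suffer from a recurrent stroke during the 12-month follow-up period will be followed-up normally", provided health allows and there is no severe aphasia. Type, location and severity of the new lesion are recorded, partly so that its effect on the outcomes can be studied. On analysis: "Recurrent strokes are taken into account in our analyses with longitudinal data to avoid confounding effects". No method is named.

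Three other places bear on this:
- **Timing of the markers.** The Discussion states that "MRI scans and venipuncture are only performed on T0".
- **Links in the background (section on vascular cognitive impairment).** Raised inflammation markers such as CRP are tied to poor prognosis: "This includes a higher risk of additional future strokes and mortality, but also more severe VCI". The list of risk factors for VCI after stroke includes "history of diabetes or atrial fibrillation, and number of recurrent strokes".
- **The question.** Study aims asks whether the markers are associated with VCI at 3 months and "predictive for its course over 12 months", with a parallel question for post-stroke depression (PSD) and apathy (PSA).

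**The concern.** A confounder must be a cause of the exposure or share a cause with it, and must not be a consequence of it. A stroke in the year after T0 comes after the markers have been measured, so the stated reason for taking it into account does not apply to those exposures.

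If a raised marker makes a further stroke more likely, and a further stroke makes VCI more likely, then recurrence carries part of the marker's association with the later course. Holding recurrence fixed, stopping follow-up at it or dropping those patients leaves only the remainder. That is a different quantity from prediction at T0, when nobody knows who will have another stroke. Conditioning on an event after baseline can also bring in bias, because recurrence and the outcome are likely to share causes that are not all measured.

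**Working it through.** **1. The plan's own figures.** Power calculation and sample size uses "a two-sided alpha level of .05", a 50/50 exposure split, 20% drop-out (250 × 0.8 = 200), and outcome rates of 50% (VCI) and 35% (PSD). A Poisson-type power formula at N = 200, with those rates in the unexposed, gives 86.1% and 78.9% for PSD (stated 86% at RR 2.00, 80% at 1.89) and 95.9% and 78.2% for VCI (stated 96% at RR 2.00, 80% at 1.70). A Wald version at N = 250, with the rates taken as overall rates, fits about as well (86.4/80.9 and 95.5/81.7). Recurrence enters neither version, so these figures do not bear on the structural point. They supply the 50% VCI rate and the design RR of 1.70 used below.

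**2. Structure.**
- Marker at T0, recurrence after T0: recurrence cannot cause the marker. This holds for every marker measured at T0.
- Marker to recurrence: stated for inflammation markers.
- Recurrence to outcome: stated for VCI.
- Both links together are therefore stated only for inflammation markers and VCI.

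**3. Size, under assumptions.** The documents give no recurrence rate and neither link's strength. Assumed:
- overall recurrence *rec* of 5–15% in the year
- marker–recurrence RR *k* of 2 or 3
- recurrence–VCI RR *m* of 1.5 or 2
- direct RR *D* of 1.40 (assumed) or 1.70 (the design value for VCI)
- half the patients exposed.

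Formulas:
- recurrence risk: unexposed r0 = 2·rec/(1 + k), exposed r1 = k·r0
- f0 = 1 + r0(m − 1), f1 = 1 + r1(m − 1)
- total RR = D·f1/f0; the adjusted analysis returns D
- share of log RR removed = 1 − ln D / ln(total RR).

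**4. Feasibility.** Taking 50% as the overall VCI rate, the risk in unexposed patients without recurrence is b = 1/(f0 + D·f1), and in exposed patients with recurrence it is b·D·m. For rec = 10%, k = 2, m = 2, D = 1.40: f0 = 1.0667, f1 = 1.1333, b = 1/(1.0667 + 1.5867) = 0.377, and the risk is 0.377 × 1.40 × 2 = 1.055, which is impossible. All six cases with m = 2 fail at D = 1.40 (1.004 to 1.108), and all six fail at D = 1.70 (1.077 to 1.194). With m = 1.5 the largest risk is 0.81–0.85 (D = 1.40) or 0.87–0.92 (D = 1.70), so those cases are kept.

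**5. Results, m = 1.5.**

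| rec | k | r0 / r1 | Total RR (D = 1.40) | Removed | Total RR (D = 1.70) | Removed |
|---|---|---|---|---|---|---|
| 5% | 2 | 3.3% / 6.7% | 1.423 | 4.6% | 1.728 | 3.0% |
| 5% | 3 | 2.5% / 7.5% | 1.435 | 6.8% | 1.742 | 4.4% |
| 10% | 2 | 6.7% / 13.3% | 1.445 | 8.6% | 1.755 | 5.6% |
| 10% | 3 | 5.0% / 15.0% | 1.468 | 12.4% | 1.783 | 8.2% |
| 15% | 2 | 10.0% / 20.0% | 1.467 | 12.1% | 1.781 | 8.1% |
| 15% | 3 | 7.5% / 22.5% | 1.501 | 17.2% | 1.823 | 11.6% |

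With rarer and weaker links (rec = 3%, k = 1.5, m = 1.5), the total RR is 1.408 or 1.710 and the share removed is 1.7% or 1.1%.

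**6. Limit of the feasibility check.** If 50% were the rate in the unexposed, even m = 1.5 with D = 1.40 would put exposed patients with recurrence at 0.5 × 1.40 × 1.5 / f0 = 1.05/f0, that is 1.00 to 1.04. The links would then have to be weaker and the loss smaller. The table is an illustration, not an estimate.

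**The case against.** **The method is not stated.** Taking recurrence into account could mean a covariate, a time-varying term, censoring or a sensitivity analysis. The same paragraph says that patients stay in follow-up and that the effect of recurrence will be studied. This stands: a reader might infer that the plan commits to covariate adjustment in the main models, and the text does not say so. What remains is that the only reason given is control of confounding, and that reason is wrong for T0 markers however the method is filled in.

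**The mediating path is not general.** A reader might infer that recurrence lies between all the markers and all the outcomes. The article does not support that. It states no full path for genetic, neurodegenerative or lesion markers, nor for PSD or PSA. Its risk-factor entry, "and number of recurrent strokes", does not separate strokes before the index event from later ones. The timing argument covers every T0 marker; the mediation argument covers one pair.

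**Recurrence can be a true confounder elsewhere.** The Discussion also plans to look at how VCI, PSD and PSA influence each other over time. A stroke between T0 and the 6-month visit can affect both mood at that visit and cognition at 12 months. This stands, so a blanket rule against adjustment would be wrong.

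**The target may be mechanistic.** An effect that does not run through a new stroke is a legitimate quantity. The wording on predicting the course favours the total association but does not settle it. A reader might therefore call the adjusted result biased towards the null; that holds only if the total association is the target. Any bias from shared causes has no size or direction that the documents allow one to derive.

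**Larger losses are not supported.** Stronger assumed links (recurrence–VCI RR 2) give up to 28% at a direct RR of 1.40, but they imply risks above 1 at a 50% overall VCI rate.

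**Conclusion.** The concern holds in limited form. Confounding is the wrong reason for handling post-T0 strokes in models of markers measured at T0. For inflammation markers and VCI, the article's background makes recurrence a plausible mediator, so conditioning on it would remove part of the association with the 12-month course. The size cannot be derived from the documents. In the feasible assumed cases it is about 3–17% of the log relative risk: 4.6–17.2% at a direct RR of 1.40 and 3.0–11.6% at 1.70. It falls to 1–2% if recurrence is rare and weakly linked. These figures rest on assumed recurrence rates and link strengths, multiplicative effects, a 50% overall VCI rate, and the method being one that conditions on recurrence.

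**What to change.** Replace the sentence in Assessments with a rule that separates two kinds of analysis:

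- **T0 markers on later VCI, PSD and PSA.** The main analysis does not adjust for, exclude or censor at recurrent stroke after T0. Strokes before T0 may be adjusted for. Recurrence is reported as a mediator, or in a secondary analysis labelled as estimating the association not acting through a new stroke.
- **VCI, PSD and PSA related to each other during follow-up.** Keep adjustment for recurrence as a time-varying term, since here it can confound.

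The cost is a sentence or two. The recurrence data are already being collected, no visits or measurements are added, and the adjusted analysis is kept under its proper label.
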